# A randomised controlled trial investigating the effect of improving the cleaning and disinfection of shared medical equipment on healthcare-associated infections: the CLEaning and Enhanced disiNfection (CLEEN) study

**DOI:** 10.1186/s13063-023-07144-z

**Published:** 2023-02-22

**Keywords:** Hospitals, Cleaning, Cross-infection, Cost-effectiveness, Shared medical equipment, Infection control, Health services, Disinfection

## Abstract

**Background:**

Healthcare-associated infections (HAIs) are a common, costly, yet largely preventable complication impacting patients in healthcare settings globally. Improving routine cleaning and disinfection of the hospital environment has been shown to reduce the risk of HAI. Contaminated shared medical equipment presents a primary transmission route for infectious pathogens, yet is rarely studied. The CLEEN study will assess how enhanced cleaning and disinfection of shared medical equipment affects the rate of HAIs in a tertiary hospital setting. The initiative is an evidence-based approach combining staff training, auditing and feedback to environmental services staff to enhance cleaning and disinfection practices.

**Methods:**

The CLEEN study will use a stepped wedge randomised controlled design in 10 wards of one large Australian hospital over 36 weeks. The intervention will consist of 3 additional hours per weekday for the dedicated cleaning and disinfection of shared medical equipment on each ward. The primary outcome is to demonstrate the effectiveness of improving the quality and frequency of cleaning shared medical equipment in reducing HAIs, as measured by a HAI point prevalence study (PPS). The secondary outcomes include the thoroughness of equipment cleaning assessed using fluorescent marker technology and the cost-effectiveness of the intervention.

**Discussion:**

Evidence from the CLEEN study will contribute to future policy and practice guidelines about the cleaning and disinfection of shared medical equipment. It will be used by healthcare leaders and clinicians to inform decision-making and implementation of best-practice infection prevention strategies to reduce HAIs in healthcare facilities.

**Trial registration:**

Australia New Zealand Clinical Trial Registry ACTRN12622001143718.

## Administrative information

Note: the numbers in curly brackets in this protocol refer to SPIRIT checklist item numbers. The order of the items has been modified to group similar items (see http://www.equator-network.org/reporting-guidelines/spirit-2013-statement-defining-standard-protocol-items-for-clinical-trials/).

## Introduction

### Background and rationale {6a}

One in 10 patients in an Australian hospital will acquire an infection while in the hospital (1). This equates to approximately 170,000 infections each year (2). These hospital-acquired infections represent just a subset of the total number of healthcare-associated infections (HAIs), which include infections associated with receiving healthcare in all settings. The burden of HAIs is significant, with increased levels of morbidity and mortality and, for those acquired in hospitals, increased length of stay (2,3). However, there is little level 1 evidence into the role of environmental cleaning to reduce HAIs (4,5). Prevention of infections through practical, implementable and translatable interventions is of critical importance in the era of antimicrobial resistance. These strategies will not only reduce the burden and impact for patients and health services in the short term, but also contribute to limiting antimicrobial resistance and better prepare healthcare settings for emerging infectious disease threats.

Contaminated healthcare environments provide a reservoir for pathogens to be transmitted to patients. Admission to a hospital room previously occupied by a patient infected and/or colonised with a specific pathogen is a major risk factor for acquisition (6). This means that a primary transmission route of pathogens is via the patient environment. A seminal study published in 2020, conducted in 11 Australian hospitals (REACH study), demonstrated improvements in routine hospital cleaning being associated with a reduction in infections (7). This research was the first cluster randomised control trial (RCT) to evaluate the effect of a cleaning and disinfection bundle that focuses on routine and discharge hospital cleaning on the incidence of HAIs. The REACH study did not, however, focus on the cleaning of shared medical equipment. This is a significant lacuna because infectious pathogens have been identified on shared medical equipment (8). Another Australian study published in 2018 demonstrated through whole genome sequencing that shared medical equipment also plays a critical role in the transmission of infection (8). This proposed trial builds on the REACH study findings, including important implementation strategies, and focuses on improving the cleaning and disinfection of shared medical equipment as a key strategy in the reduction of HAIs.

## Objectives {7}

Objective 1: Assess the effectiveness of improving the quality and frequency of cleaning and disinfection of shared medical equipment in reducing HAIs.

Objective 2: Evaluate the cost-effectiveness of the intervention.

## Trial design {8}

This study is a stepped wedge randomised controlled study, conducted in 10 wards of one acute Australian hospital over 36 weeks. A stepped wedge design allows all wards to receive the intervention at different times, with each ward acting as its own control. Each cluster will comprise two wards. One cluster will switch to the intervention every 6 weeks. This study design reduces the influences of confounders such as variations in size and case mix and supports feasibility while maintaining rigour. This design also allows research staff to work with individual wards as they adopt the intervention, maximising consistency of intervention and aiding implementation (Fig. 1).

**Fig. 1 Fig1:**
[figure not shown]
The stepped wedge study design. Green (dotted) = control, blue (striped) = intervention

## Methods: participants, interventions and outcomes

### Study setting {9}

One Australian hospital that meets the eligibility criteria will be enrolled in the study. Ten wards within the hospital will be selected for the study.

### Eligibility criteria {10}

The eligible hospital will meet the following criteria: classified as a ‘Public acute group A hospital’ by the Australian Institute of Health and Welfare (9), located in New South Wales, have an intensive care unit, have a minimum of 10 wards, and caring for adult patients (i.e. ≥ 18 years old) willing to participate in the study. Ten wards with > 20 beds, caring for adult patients, will be selected for the study.

Hospitals will be excluded from the study if they do not meet the inclusion criteria. Hospitals may also be excluded from the study if within the study time frame (2023–2024) they are opening, closing or relocating, or implementing major environmental cleaning initiatives or changes.

### Who will take informed consent? {26a}

This project collects data associated with human beings only. Data from all patients (> 18 years old) who are inpatients on one of the 10 wards on the day of the PPS will be used. As this project collects data associated with human beings only, there is no consent process and a waiver of consent has been sought and granted by the authorising Human Research Ethics Committee (HREC). The approach taken in this study with respect to a waiver of consent is consistent with other multi-centre studies where a point prevalence study of healthcare-associated infections has been undertaken as the primary outcome (and data collection method) and ethics approval has been granted (1,10,11). Similarly, our approach is consistent with stepped wedge trials with infections as the outcome and interventions that posed low risk and collected data from existing records. In these instances, a waiver of consent was granted.

There are no interventions and no harm or discomfort to the patient as a result of the project. The benefits of the research justify any risk of harm associated with not obtaining consent. Results of the research are not individualised or patient identifiable. The study requires no direct involvement of patients; rather, it collates existing information obtained during their hospitalisation. No new information will be obtained about individual patients; therefore, results will have no significance for the individual welfare of patients.

### Additional consent provisions for collection and use of participant data and biological specimens {26b}

Not applicable—no biological specimens will be collected for this study.

## Interventions

### Explanation for the choice of comparators {6b}

The stepped wedge study design allows each ward to act as its own control. During the control phase, the cleaning and disinfection of shared medical equipment are undertaken by PSAs according to hospital policies. The intervention phase introduces 15 additional hours per week, purely dedicated to the cleaning and disinfection of shared medical equipment. During the intervention phase, PSAs will be educated on correct cleaning and disinfection technique. To confirm equipment is being properly cleaned during the intervention, auditing with fluorescent markers (FM) will allow feedback to PSA staff. This design allows the comparison between routine (control) and enhanced (intervention) disinfection.

### Intervention description {11a}

The intervention will consist of additional time dedicated to cleaning and disinfection of shared medical equipment, education on cleaning technique, auditing of cleaning efficacy and feedback on cleanliness to staff. This multimodal strategy to improve the cleaning and disinfection of shared patient equipment is grounded in the literature and recent research (7,12). The primary target for the intervention is the cleaning staff.

#### Additional cleaning

During the intervention phase, each trial ward will receive an additional 3 h of cleaning per weekday by dedicated cleaners. This is in addition to routine cleaning that already occurs. The use of dedicated cleaners will reduce the risk of contamination and assist in consistency in implementation. An expression of interest process will be used to identify cleaners who are seeking additional work. This will be managed and handled by the participating hospital, in line with enterprise bargaining arrangements and local policy.

The additional cleaning will focus on specific shared medical equipment (Table 1). The use of a Therapeutic Goods Administration (TGA)-registered dual detergent-disinfectant wipe effective against a range of bacteria and viruses will be used for additional cleaning. The fidelity of the additional cleaning will be measured using the fluorescent markers (see the ‘Audit and feedback’ section). In addition, items that have been cleaned but remain in storage until use will be labelled as cleaned, using bright labelling. This will enable clinical staff to easily identify which equipment is clean and ready for use.

**Table 1 Tab1:** Focus of additional cleaning

Type of equipment	Additional detail	Frequency	Estimated time
Intravenous drip stand/pole	Those in use by patients	Daily	5 min
	Those in the storage on the ward	Daily	10 min
Infusion pump(s)	Those *not in use* by patients. Areas to be cleaned include all external surfaces daily	Daily	10 min
Mobile blood pressure machines	Automatic machines Areas to be cleaned are cuff, buttons, O_2_ probe, temperature probe, and storage basket	Daily	30 min
Computer on wheels (approx. 10–15 per ward)	Surfaces to be cleaned include: • Horizontal surfaces • Keyboards • Vertical surface and pedestals	Daily Daily Weekly	60 min
Commodes	All surfaces to be cleaned, focus on handles and seat	Daily	20 min
Blood glucose machine	Machines include those in a box and the smaller glucose machines. Focus on cleaning surfaces	Daily	10 min
Mobility equipment	Focus on cleaning frequency touch areas, e.g. handles. Those in storage/shared areas, i.e. not those kept in patient rooms	Daily	20 min
Total			165 min

^Note that if time allows, other equipment will include trolleys, bladder scanners (cleaning probe and buttons), patslides (those in shared areas/storage only), resuscitation trolleys (top surface and drawers—outside only) and medication trolleys

#### Education

The dedicated cleaners undertaking the additional cleaning will undergo education and training sessions prior to the commencement of the intervention. Education prior to the invention will include at least a 1-h in-service, where cleaning techniques will be taught and practised. This will occur no longer than 2 months prior to the commencement of the intervention. The training will be delivered by staff experienced in education and cleaning practice. Standard operating procedures for cleaning specific items of shared medical equipment will be developed and subsequently explained at the in-service (if they are not already in existence at the hospital). These will also be readily available for staff for future reference as needed.

#### Audit and feedback

The benefits and role of audit, including the use of fluorescent markers (FM), in assessing environmental cleaning, is well documented (7,13,14). Audit and feedback to the cleaning staff involved in the additional cleaning will include the use of FM technology, in which invisible gel dots that are removed by cleaning are applied to surfaces. The dots are invisible to the naked eye, resist dry abrasion, and are removed completely by routine cleaning. A structured auditing approach, with staff feedback underpinned by education, will aid improvements in cleaning, as shown in multiple studies (7,13,14). FM auditing of shared equipment will be conducted fortnightly in each ward.

During the intervention phase, audit results will be reported verbally to the cleaning staff, with a follow-up email to cleaning supervisors and the Nursing Unit Managers. Audit results will be used to inform further informal face-to-face education and training. In discussing audit results, informal goals for the next audit will be set with the cleaners. Additional reports will be provided for internal committees, such as the Infection Prevention and Control committee at the conclusion of the study.

### Criteria for discontinuing or modifying allocated interventions {11b}

The study will be discontinued if a regulatory body, funding body or the HREC judges it necessary for medical, safety, regulatory or other reasons consistent with applicable laws, regulations and good clinical practice.

### Strategies to improve adherence to interventions {11c}

To improve adherence to intervention protocols, there will be educational training sessions that focus on correct cleaning techniques. Refresher training sessions for PSAs will be held during the intervention period to promote correct cleaning and disinfection techniques. The study coordinator will have regular communication with PSAs (fortnightly) where the results of the FM audits will be communicated to PSA staff to help improve the quality of cleaning and disinfection. During the intervention phase, PSAs allocated to additional cleaning hours will have daily communication with Nursing Unit Managers.

### Relevant concomitant care permitted or prohibited during the trial {11d}

Not applicable—as there is no direct intervention for patients.

### Provisions for post-trial care {30}

Not applicable—as there is no intervention directly to participants. The intervention, additional hospital cleaning, carries no additional risk to participants.

### Outcomes {12}

The primary outcome is the proportion of inpatients aged ≥ 18 years old with a HAI as measured by a HAI point prevalence study (PPS). The secondary outcomes are the thoroughness of cleaning as being the proportion of dots that were completely removed, as measured by the FM gel and ultraviolet light system, and the cost-effectiveness of the intervention compared with routine cleaning.

### *Participant timeline**{13}*

The participant timeline is shown in Fig. 2.

**Fig. 2 Fig2:**
[figure not shown]
Timeline for enrolment, interventions and assessments of the study. FM fluorescent markers, HAI healthcare-associated infection

### Sample size {14}

The study design ensures a sample size sufficient to detect a relative reduction of at least 35% in total HAI infection, with a baseline point prevalence of 11%. It is powered at 80%, based on a two-sided 5% significance level with an inter-cluster correlation of 0.3 and coefficient of variation of 0.65—allowing for variation in cluster size. A stepped wedge sample size formula was used, considering the number and size of clusters and the time period. The required cluster size is 132 (66 per ward), achieved with two wards forming clusters and three fortnightly PPS each time period (*n* = 3960—5 clusters, 6 time periods). The baseline infection rate was determined using recently published work by the applicant and reductions identified in a recent RCT (3,15). Varying the intra-cluster correlation between 0.2 and 0.5 produced minimum sample sizes per cluster period of 94 (47 per ward) to 150 (75 per ward).

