To reduce the effect of confounders due to seasonality, viral respiratory infections (RSV, COVID-19, influenza) will be removed for the purpose of primary analysis. In addition, any HAI data related to an outbreak will be excluded from primary analysis. The study period is aligned to span over three full seasons (autumn, winter, spring), with the study midpoint corresponding to the usual epidemiological peak for respiratory infection in the region. Additionally, the use of historical coding data can identify underlying trends over recent years.

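### The 80% power is stated for total HAI at an 11% baseline, but the primary analysis removes viral respiratory and outbreak HAIs, so the stated power is not for the outcome tested

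*Protocol article*

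**What the plan says.** **Power statement (Sample size {14}).** The design is described as "sufficient to detect a relative reduction of at least 35% in total HAI infection, with a baseline point prevalence of 11" per cent. The text continues "It is powered at 80" per cent, "based on a two-sided 5% significance level with an inter-cluster correlation of 0.3 and coefficient of variation of 0.65". On size it says: "The required cluster size is 132 (66 per ward), achieved with two wards forming clusters and three fortnightly PPS each time period", for a total of 3960 ("3960—5 clusters, 6 time periods"). Varying the ICC from 0.2 to 0.5 "produced minimum sample sizes per cluster period of 94 (47 per ward) to 150 (75 per ward").

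**Outcome analysed (Primary outcome analysis, under {20a}).** The section first describes the fortnightly count as HAIs of every type taken together. It later says that "viral respiratory infections (RSV, COVID-19, influenza) will be removed for the purpose of primary analysis", and that HAI data connected with an outbreak are also left out of the primary analysis.

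**Attribution (Plans for assessment and collection of outcomes {18a}).** An HAI counts for a ward only if symptoms began more than 48 hours after admission to that ward. One identified within 48 hours of a transfer is assigned to the previous ward.

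**Ward size (Eligibility criteria {10}).** "Ten wards with > 20 beds, caring for adult patients, will be selected for the study".

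**The concern.** The power calculation and the primary analysis should refer to the same outcome. Here the first is expressed for total HAI, and the second drops two groups of HAI. The Sample size section does not say that the 11% or the 35% is net of those removals. Removing events can only lower the prevalence. The amount may matter, because the protocol places the study midpoint at the usual respiratory-infection peak. The 48-hour rule may take away a few more, where the previous ward is outside the ten.

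At stake is the reading of the result. With a fixed number of patients and a fixed relative effect, a rarer outcome means less power. If the trial is null, readers will set that against an 80% claim made for a different outcome.

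**Working it through.** **Inputs from the Sample size section.** Baseline p0 = 0.11; relative reduction 35%, so p1 = 0.11 × 0.65 = 0.0715 and the difference is 0.0385; two-sided alpha 0.05; power 80%; ICC 0.3; 5 clusters, 6 periods, 132 per cluster-period (5 × 6 × 132 = 3960).

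**Step 1: reproduce the 132.** The individually randomised size per arm is (1.960 + 0.842)² × [0.11 × 0.89 + 0.0715 × 0.9285] / 0.0385² = 870. The Woertman stepped-wedge design effect, with k = 5 steps, b = 1 baseline period and t = 1 measurement per step, is

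DE = [1 + ρ(kn + bn − 1)] / [1 + ρ(kn/2 + bn − 1)] × 3(1 − ρ) / [2(k − 1/k)].

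At ρ = 0.3 and n near 130, DE = 0.374. Size per cluster-period = 2 × 870 × 0.374 / 5 ≈ 130, against the stated 132. The same formula gives 149 at ICC 0.2 (stated 150) and 93 at ICC 0.5 (stated 94). The plan's arithmetic therefore holds for its own inputs. The match needs no inflation for the coefficient of variation.

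**Step 2: cross-check by Hussey–Hughes variance.** Let s be the mean of p0(1 − p0) and p1(1 − p1), σ² = s(1 − ρ)/n and τ² = sρ. For 5 clusters and 6 periods the design sums are U = 15, W = 55, V = 55, so

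Var = 5σ²(σ² + 6τ²) / (20σ² + 70τ²).

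With s = 0.08214: σ² = 0.000436, τ² = 0.02464, SE = 0.01365. Then 0.0385 / 0.01365 − 1.960 = 0.861, and power is 80.5%.

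**Step 3: lower the baseline and keep everything else.** The prevalence left after the removals is not in the documents, so the rows below 11% are assumptions. The 35% relative reduction is held constant, which is also an assumption.

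| Baseline | With intervention | SE | Power at 132 | Size per cluster-period for 80% | Relative reduction detectable at 132 with 80% power |
|---|---|---|---|---|---|
| 11% | 7.15% | 0.01365 | 80.5% | 130 | 34.8% |
| 10% | 6.50% | 0.01308 | 76.3% | 145 | 36.5% |
| 9% | 5.85% | 0.01246 | 71.5% | 162 | 38.5% |
| 8% | 5.20% | 0.01181 | 66.0% | 184 | 40.7% |
| 7% | 4.55% | 0.01109 | 59.8% | 213 | 43.3% |

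Each percentage point off the baseline costs about 4 to 6 points of power.

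**Step 4: let the relative effect change.** Suppose that total HAI does fall by 3.85 points from 11%, and that none of the removed infections respond to cleaning. The whole 3.85 points then falls on the HAIs that remain. From 9%, that is a relative reduction of 3.85 / 9 = 43%, and the Step 2 formula gives 88.5% power at 132. Under this assumption there is no loss.

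**Step 5: ward size.** 66 per ward-period over three surveys is a mean of 66 / 3 = 22 counted patients per ward per survey. The smallest ward allowed has 21 beds: 3 × 21 = 63 when full, or 126 per two-ward cluster-period. If all ten wards were that size and always full, power at 11% would be 78.7%.

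**The case against.** The strongest reply is that the shortfall depends on sources that are not shown. The 11% comes from cited published work, and the protocol does not say whether that figure already leaves out viral respiratory or outbreak infections. If it does, the power stands and only the word total is wrong. This is fair, and it limits what can be said about size. It does not remove the mismatch, because both descriptions of the outcome are in the text and they differ.

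Second, the losses in Step 3 hold the relative effect at 35%. Step 4 shows that another reasonable assumption reverses the direction. This stands. A reader might infer that the trial is underpowered, or that the plan's inputs err only in its favour; the documents do not support either inference.

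Third, a reader might take the Background's statement that one in 10 patients acquires an infection as evidence of a lower baseline. It is an acquisition risk rather than a point prevalence, and the same paragraph calls those infections a subset of all HAIs, so it says nothing against 11%.

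Fourth, the 48-hour rule partly moves infections between wards rather than deleting them. That is correct. Only those sent to a ward outside the ten are lost, so the removals in the Primary outcome analysis section carry the weight.

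Fifth, the bed count is a floor for eligibility, not an expected size. A mean of 22 is enough, and larger wards offset smaller ones. A reader might infer that the ward rule leaves the sample materially short. The text does not show that: even with every ward at 21 full beds, power falls by less than 2 points.

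**Conclusion.** The point holds as an inconsistency between the powered outcome and the analysed outcome. It is not an arithmetic error, since the stated 132 and its ICC range both reproduce. Taken as written, the 80% belongs to total HAI at 11% and does not carry over to the outcome after the removals.

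The size cannot be fixed from the documents. With 132 per cluster-period, ICC 0.3 and a constant 35% relative reduction, power would be between about 76% and 60% for an assumed post-removal baseline of 10% down to 7%. If the removed infections are unaffected by cleaning, the loss would be smaller or absent. Because 132 gives almost no margin above 80%, the choice between these assumptions decides whether the claim is met.

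The ward-size rule is a minor secondary matter: it does not guarantee the planned sample, but at full occupancy the effect on power is under 2 points.

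**What to change.** 1. In the Sample size section, state the baseline prevalence and the target effect for the outcome as analysed, after the viral respiratory and outbreak removals. If the 11% and 35% already refer to that outcome, say so and drop the word total.
2. Restate the power, or the reduction detectable with 80% power, for that outcome over a range of baselines (for example 7% to 11%) and at the eligible 08:00 census of the wards selected. Say whether the relative or the absolute effect is held constant.
3. In the Primary outcome analysis section, reconcile the description of the outcome as every HAI type combined with the removals that follow it.
4. Soften the claim that the design ensures the sample size. Say instead that it relies on a mean of about 22 counted patients per ward per survey.

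The cost is wording and one recalculation, with no extra patients or surveys. The stated power may become less favourable.

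### The stated 80% power rests on a favourable, unsourced intra-cluster correlation of 0.3 and does not appear to include the cluster-size variation it claims to allow for

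*Protocol article*

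**What the plan says.** The section Sample size {14} of the protocol article sets the target, which is to "detect a relative reduction of at least 35% in total HAI infection", "with a baseline point prevalence of 11"%. The error rates and clustering assumptions follow: "It is powered at 80%, based on a two-sided 5% significance level with an inter-cluster correlation of 0.3 and coefficient of variation of 0.65". The last figure is given a purpose: "coefficient of variation of 0.65—allowing for variation in cluster size".

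The planned size is 132 patients per cluster-period (66 per ward), with 5 clusters and 6 periods, 3960 in all. The sensitivity statement reads "Varying the intra-cluster correlation between 0.2 and 0.5 produced minimum sample sizes per cluster period of 94 (47 per ward) to 150" (75 per ward).

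The section cites sources for the baseline rate and for the reduction. It gives none for the correlation of 0.3, and no result for any correlation below 0.2.

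**The concern.** In a parallel cluster trial a large intra-cluster correlation (ICC) is the cautious choice, and a reader will take 0.3 in that spirit. In a stepped wedge analysed with a cluster random intercept, most of the information comes from comparisons within clusters. With total variance held fixed, a larger ICC leaves less variance within clusters, so beyond a small value it raises power. An ICC of 0.3 with a tested range of 0.2 to 0.5 therefore never examines the region where this design is weakest.

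The section also says that unequal cluster sizes were allowed for. If they were not, power is overstated even at the stated ICC.

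What is at stake is how a null result is read. It would be taken as 80%-powered evidence against a 35% reduction, when the chance of missing such a reduction may be nearer 30% than 20%.

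**Working it through.** **Inputs from the protocol article.** Control prevalence 0.11; 35% relative reduction, so 0.11 × 0.65 = 0.0715 and a difference of 0.0385; two-sided 5%; 5 clusters, 6 periods, one cluster switching per step (Trial design {8}); m = 132 per cluster-period.

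**Formula (Hussey-Hughes, equal sizes, categorical periods, time-constant cluster effect).**
- Mean prevalence (0.11 + 0.0715)/2 = 0.09075; total variance 0.09075 × 0.90925 = 0.08251.
- τ² = ICC × 0.08251; s = (1 − ICC) × 0.08251 / m.
- With I = 5, T = 6, U = 15, W = 55, V = 55: IU − W = 20 and U² + ITU − TW − IV = 225 + 450 − 330 − 275 = 70.
- Var = 5s(s + 6τ²) / (20s + 70τ²); power = Φ(0.0385/√Var − 1.96).

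**Step 1: reproduce the plan.** At ICC 0.3, τ² = 0.02475 and s = 0.05776/132 = 0.0004376. Var = 0.0001871, standard error 0.01368, ratio 2.814, power Φ(0.854) = 80.4%. Solving for m at exactly 80% power and rounding up to whole patients per ward:

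| ICC | m needed | per ward | size printed |
|---|---|---|---|
| 0.2 | 149.3 | 75 | 150 |
| 0.3 | 130.8 | 66 | 132 |
| 0.5 | 93.5 | 47 | 94 |

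All three printed sizes come out with equal clusters. The coefficient of variation (CV) of 0.65 is not needed for any of them.

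**Step 2: apply the CV.** With gamma-distributed cluster sizes of CV 0.65 (4000 draws, same total), mean power at ICC 0.3 is about 77%. A second illustrative set of five sizes with CV 0.65, averaged over all orders of allocation, gives about 76%.

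**Step 3: vary the ICC at the planned size (132, equal clusters).**

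| ICC | power | m for 80% |
|---|---|---|
| 0.001 | 79.5% | 135 |
| 0.01 | 69.0% | 175 |
| 0.02 | 67.9% | 178 |
| 0.05 | 68.2% | 176 |
| 0.10 | 70.2% | 168 |
| 0.20 | 75.0% | 150 |
| 0.30 | 80.4% | 131 |
| 0.50 | 91.4% | 94 |

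Power is U-shaped: 86.9% at ICC 0, a minimum of about 68% near 0.02 to 0.03, and back to about 80% only at roughly 0.001 or below, or 0.3 or above. Over ICC 0.01 to 0.10 the reduction detectable with 80% power is 39% to 40%. Treating the ten wards of 66 as the clusters gives 68.9% to 71.5% over the same range and 80.4% at 0.3, so the choice of unit matters little.

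**Step 4: what an ICC of 0.3 means.** Between-cluster SD = √(0.3 × 0.11 × 0.89) = 0.171, or 17 percentage points around a mean of 11. Under a beta distribution, 39% of clusters would have a prevalence below 1% and 13% above 30%.

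**The case against.** **The sensitivity range is not wrong.** A reader might infer that the section attaches 94 to ICC 0.2 and 150 to ICC 0.5, which would be backwards. The text does not say so. It gives two ranges, each from low to high, and both are numerically right. This is an ambiguity worth a phrase, not an error.

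**A low ICC is an assumption.** The document gives no ICC below 0.2, and its cited sources are not at hand. A flat statement that the trial has 68% to 70% power would go too far, as would a statement that 80% is reached only at 0.3, since power recovers at very small ICCs. This stands, and the range 0.01 to 0.10 is labelled as an assumption here. The 75% at ICC 0.2 needs no such assumption. In fairness, the section does print the larger size of 150.

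**132 is a required minimum.** It corresponds to 66/3 = 22 patients per ward per survey. All eligible inpatients are surveyed, on wards with more than 20 beds. At an assumed 25, 28 or 30 eligible patients per ward, the cluster-period size is 150, 168 or 180, and power at ICC 0.05 becomes 73.6%, 78.2% or 80.9%. This is fair, but bed numbers are not given, and the power claim is made for 3960.

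**The CV may have entered in another way.** No formula is named, so its omission is inferred from the exact match, and the effect at ICC 0.3 is about three points. A reader might instead take 0.65 as the between-cluster CV of prevalence, which would imply an ICC of (0.65 × 0.11)²/(0.11 × 0.89) = 0.052. The section ties 0.65 to cluster size, so the documents do not support that reading.

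**Conclusion.** The point stands in this form. The printed 80% is correct for equal clusters at ICC 0.3, but the section claims an allowance for unequal sizes that its own figures do not appear to contain; with it, power is about 77%. The ICC of 0.3 is unsourced in the article, favourable to the design over the tested range, and hard to credit for adult wards of one hospital, given the spread in prevalence it implies. At the protocol's own lower bound power is 75%. Under the stated assumption of an ICC between 0.01 and 0.10, it is about 68% to 70%.

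These figures assume a time-constant cluster effect, variance taken at the mean of the two prevalences (the version that reproduces 132) and exactly 132 per cluster-period. The first is itself favourable: with a cluster autocorrelation of 0.95, power at ICC 0.3 falls to about 30%, and at ICC 0.01 to 0.05 it is 56% to 67%.

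**What to change.** Reword the sample size paragraph, without enrolling more patients:

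- State power for a 35% reduction at the planned 3960 observations over an ICC range that extends below 0.2, for example 79.5% at 0.001, 69% at 0.01, 68% at 0.05, 70% at 0.10, 75% at 0.20 and 80% at 0.30. Add that a reduction of about 40% is detectable with 80% power at ICC 0.01 to 0.10.
- Give the basis for 0.3, or say that it is an assumption, and note that over 0.2 to 0.5 a higher ICC lowers the required size.
- Either apply the CV of 0.65 and report the resulting power, or delete the statement that variation in cluster size was allowed for.
- As a clarification, say that 150 belongs to ICC 0.2 and 94 to ICC 0.5.

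Design, enrolment and analysis are unchanged. The cost is a less favourable stated power.
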